## Abstract

**Background:**

Child mental health disorders are a significant Australian public health issue with high prevalence rates compounded by inequitably higher rates for those living in families with lower income, lower levels of parental education, and higher levels of unemployment. Prevention and early intervention approaches are critical to address problems early. When caregivers seek information and services to support their child’s mental health needs, they commonly use many untested online search strategies. To address this, we developed a digital Child and Family eHub (eHub) prototype through a user-centered design process involving families experiencing adversity and local service providers. The eHub provides online navigation and evidence-based information for families and aims to increase equitable access to and use of (1) information and (2) the existing primary health, mental health, and social services system to improve mental health outcomes for caregivers with children aged 0-12 years. This protocol outlines how we will evaluate the eHub.

**Objective:**

This study aims to evaluate the feasibility, acceptability, appropriateness, and preliminary impact of the eHub digital platform for caregivers of children aged 0-12 years, particularly those experiencing adversity. The evaluation will assess implementation outcomes, caregiver and child mental health outcomes, and help-seeking behaviors over a 6-month period.

**Methods:**

A prospective cohort of 270 caregivers of children aged 0-12 years will be recruited from 3 socioeconomically diverse Australian sites (Wyndham Vale in Victoria and Marrickville and Fairfield in New South Wales). Participants will be recruited through local community hubs, health and social service providers, and social media, and will enroll via the REDCap (Research Electronic Data Capture; Vanderbilt University) survey platform. A mixed methods type 3 implementation impact evaluation will be undertaken, which tests an implementation strategy while observing and gathering information on the intervention’s impact on relevant outcomes. In this protocol, implementation will be assessed as a primary outcome using Proctor’s outcomes for the implementation framework, and secondary outcomes will include caregiver access and use of the eHub and associated child and parent mental health outcomes. Data will be collected at baseline and 6 months. Quantitative data will be analyzed using descriptive statistics and regression models; repeated measures will be analyzed using generalized estimating equations. Qualitative data will be analyzed using framework analysis.

**Results:**

The study was funded in December 2021. Participant enrollment for the study began in February 2024, with participants involved in the eHub evaluation for 6 months.

**Conclusions:**

The results of this study will be instrumental in refining the intervention for future scaling to other Australian sites. This study has the potential to offer an accessible, cost-effective, and scalable digital solution to improve service navigation and mental health outcomes for children and families experiencing adversity.

**Trial Registration:**

ISRCTN Registry ISRCTN49839991; https://doi.org/10.1186/ISRCTN49839991

**International Registered Report Identifier (IRRID):**

DERR1-10.2196/72548

## Introduction

### Current Mental Health Concerns

Consistent with other international research [1,2], 1 in 7 Australian children aged 4-11 years reports mental health disorders in a year, with attention-deficit/hyperactivity disorder and anxiety being the most reported disorders [3]. Additionally, regulatory problems, such as excessive crying, sleeping, or feeding problems in infancy, are known predictors of later behavioral and mental health problems [4], with the Australian prevalence rates for 1 or more of these regulatory problems in infants between 7.3% and 25.2% [5]. The distribution of mental health disorders, however, is inequitable, with much higher rates in children and adolescents associated with lower socioeconomic status of families, lower levels of parental education, and higher levels of unemployment. Recent Australian national data identify additional mental health burden on children and their parents as a result of COVID-19 [6], with 50% of parents reporting their children as anxious [7], and even higher rates among children from families experiencing financial distress [8]. These data reinforce the urgent need to implement effective and equitable prevention and early intervention strategies to mitigate the continuing and unequal rise in child mental health issues.

### Early Intervention

Investing in innovative prevention and early intervention approaches is time critical for the following reasons: (1) despite increasing Australian government investment in mental health services (eg, over US $1.7 billion nationally in 2018-2019 to enhance community mental health services) [9], existing services are unable to meet the growing demand for children’s mental health, and there has not been a detectable reduction in the prevalence of psychological distress for youths [10]; (2) only 9%-27% of young children experiencing emotional and externalizing problems access Medicare-rebated services, with the lowest rates among families of low socioeconomic status or single parents and those with English as a second language [11]; (3) failing to intervene early costs the government (US $10.7 billion) annually [9]; and (4) there is currently strong policy commitment for mental health including the National Child Mental Health and Wellbeing Strategy [12].

To increase the efficiency of the support systems, we need to make better use of the existing (and already funded) health and social care system. In a National Child Health poll of 2000 Australian parents prior to COVID-19, only 44% reported feeling confident that they would know where to go for professional help if their child was experiencing social, emotional, or behavioral difficulties [13]. Indeed, caregivers often feel overwhelmed by the amount and complexity of information and need accessible, reliable, and relevant support to guide them through the process of accessing services relating to their child’s social, emotional, and behavioral problems [14]. Rather than looking for mental health services per se, caregivers seek practical tips, connections to a range of services, and reassurance of the best approach to take with their family and child’s mental health. These findings were recently corroborated ([name], PhD, unpublished data, January 2024). Low levels of access and use of community and mental health services are thought to be due to a combination of barriers including financial, cultural, transport, and health literacy barriers [15]. The process of navigating a complex community and mental health service system leads to inequities in access, missed (and costly) opportunities for early intervention, and subsequent inequities in outcomes for children.

### Caregivers’ Current Help-Seeking Behavior and Use of Information and Services

Caregivers already use a range of digital search strategies and social media to seek information and services to support their child’s health needs. These findings were recently corroborated ([name], PhD, unpublished data, January 2024). Common challenges for caregivers seeking online information or services are too much or not enough relevant or trusted information, lack of time to source information or services, a sense of burden felt by caregivers to find an appropriate solution, and getting “stuck” and unsure how to progress seeking appropriate support. Caregivers report that they want to find practical actions to resolve their concerns or issues, connect with existing technologies and services, and not feel judged. These findings were recently corroborated ([name], PhD, unpublished data, January 2024).

### Digital Solutions

Digital solutions offer great potential to provide high reach, low stigma strategies to deliver information, programs, and services [16], which can be tailored to a family’s needs. While there are many digital apps and platforms available, very few have been developed for children aged 0-12 years and their families or specifically offer service navigation support for childhood adversities or their associated mental health problems [17]. Adversities include childhood maltreatment (eg, physical, verbal, or sexual abuse) and household dysfunction (eg, parental mental illness and family substance abuse) [18] as well as broader social determinants of health—nonmedical factors that influence health outcomes, including the conditions in which people are born, grow, work, and live [19].

To address this need, our team has developed a prototype or minimum viable product (MVP) for a digital Child and Family eHub (eHub) using a user-centered design process. The process involved local service providers and caregivers experiencing adversity. The eHub aims to optimize caregiver information and local service-seeking experience and satisfaction. The user-centered design process for the eHub is outlined in previous research. The eHub connects caregivers to evidence-based information and a range of health, education, justice, and social services to support broader adversities families experience. The eHub (1) is tailored to the specific needs of caregivers with young children aged 0-12 years; (2) is designed to deliver varying levels of supported navigation based on individual need or capacity; and (3) addresses specific issues related to the social determinants of health, diversity, and reach. Improving access to information, services, and supports we hypothesize will lead to improved and more equitable mental health outcomes for children.

### Objectives

This protocol details the methods to evaluate the primary and secondary outcomes of the eHub for caregivers with children aged 0-12 years, with a specific focus on populations with low education, diverse languages, and socioeconomic deprivation. We will undertake a type 3 implementation impact evaluation as defined by Curran et al [1]. Type 3 implementation impact evaluation tests an implementation strategy while observing and gathering information on the intervention’s impact on relevant outcomes. In this protocol, implementation will be assessed as a primary outcome using Proctor’s outcomes for the implementation framework [20]. Secondary outcomes will include family information and service access and use, as well as child and caregiver mental health.

## Methods

### Study Design

A multisite type 3 mixed methods hybrid implementation or impact evaluation will be conducted [1]. The approach will assist in understanding access and use of the eHub by caregivers via the collection of users’ data analytics on the eHub platform and via a prospective cohort sample, which will provide a “deep dive” into factors affecting caregiver access and use of the eHub and associated child and caregiver mental health outcomes. Quantitative (survey) and qualitative (semistructured interview) data will be collected in parallel and integrated during data analysis and interpretation. This protocol was informed by the Standards for Reporting Implementation Studies framework [21], and where relevant, it incorporates principles from the SPIRIT (Standard Protocol Items: Recommendations for Interventional Trials) 2013 checklist.

### Site Selection

eHub sites were chosen based on populations experiencing several adversities—as defined via low socioeconomic status, cultural diversity, child vulnerability, unemployment, and low education levels. Sites in Australia include Marrickville and Fairfield in Sydney and Wyndham Vale in Melbourne (Table 1). To note, the Marrickville suburb experiences significant pockets of disadvantage among areas of advantage. These 3 sites also had an existing physical Child and Family Hub within the local service system, which integrated health and social care for children and their families.

**Table 1 table1:** Sites involved in evaluation.

State	Site	Population details^a^				
		Socio-Economic Index for Area^b^	Australian Early Development Census—Children vulnerable in 1 domain (national comparison: 22%) (%)	Population 15+ years unemployed (national comparison: 5.1%) (%)	Population completed year 12 or equivalent (national comparison: 51.9%) (%)	Population born overseas (national comparison: 27.7%) (%)
Victoria	Wyndham Vale	972 (second quintile)	24.2	7.3	48.8	40.1
New South Wales	Marrickville	1050 (fourth quintile)	15.5	4.7	64.9	35.1
New South Wales	Fairfield	838 (first quintile)	28.6	8.7	48.2	56

^a^Percentage proportions reported for comparison as the population size varies across sites.

^b^Socio-Economic Index for Area is a group of 5 indexes that provides a relative measure of socioeconomic advantage and disadvantage for small geographic areas; 1000 is the average, lower scores indicate more disadvantage, first quintile=most disadvantaged.

### Child and Family eHub MVP

The eHub MVP was developed using user-centered design with caregivers and local service providers and aims to support and guide caregivers through a local, proportionate approach including increasing tiers of support. These tiers, outlined in Figure 1, include self-navigation for all families (tier 1) through to guided chatbot technology and finally, human navigator assistance, which has been shown to be effective [22] for those most in need (tier 4). Figure 1 also includes a brief overview of each tier of the eHub. Caregivers determine the level of support they need based on their ability to find and access information and services that suit their family needs. Each caregiver enters the eHub at tier 1 and progress to additional tiers based on their needs, for example, filtering topics or geographic areas to find appropriate information or local services (tier 2), using a chatbot to assist with defining the mental health topic most suitable to their needs (tier 3), or speaking to a personal navigator to understand the child’s or families’ specific information or service needs and assist with navigation to services (tier 4). It is anticipated that 90%-95% of eHub users will interface with tiers 1-3 based on theories of proportionate universalism [23,24], with only 5%-10% of users requiring the more intensive element of the eHub personal navigator.

**Figure 1 figure1:**
[figure not shown]
Tiers of support provided through the eHub. eHub: Child and Family eHub.

### Recruitment

#### Prospective Cohort of Caregivers

The study will recruit 270 caregivers of children aged 0-12 years from the 3 identified sites (Table 1). To ensure representation of caregivers experiencing a range of adversities, the eHub will be advertised widely in the community in each site through posters and flyers with QR codes at physical primary care, community health and nongovernment organization hub sites, local community groups, schools, parent groups, playgroups, and social media to recruit caregivers with children aged 0-12 years. Interested caregivers will follow the QR code link to REDCap (Research Electronic Data Capture; Vanderbilt University)—a secure, web-based data capture platform hosted by the research team, where they can watch an informational video about the study and provide informed consent to be involved. Caregivers will then complete a baseline survey for the evaluation, including whether they meet the inclusion criteria (listed below); this will be our prospective cohort sample of caregivers. If caregivers respond “no” and would prefer not to participate in the evaluation, they can continue to use the eHub. eHub data analytics will be collected on all users of the eHub, including those involved in the evaluation and those who are not. Those not involved in the evaluation will not require consent to participate, as all eHub data analytics collected will be unidentifiable. Demographic details of participants will be collected through pop-up surveys on the eHub site. Figure 2 outlines the caregiver journey through the evaluation. Recruitment for the evaluation commenced in February 2024 and continued for each caregiver involved for 6 months.

The caregiver inclusion criteria are as follows: parents or primary caregivers with at least 1 child aged 0-12 years, noting that only 1 primary caregiver per family unit can enroll in the evaluation study; live in eligible intervention sites (Marrickville and Fairfield in New South Wales or Wyndham Vale in Victoria); can speak sufficient English to participate in the study and complete the survey, noting that although each of the study sites are culturally diverse, many residents speak English; and provide informed consent.

**Figure 2 figure2:**
[figure not shown]
Caregiver journey for the evaluation trial. eHub: Child and Family eHub; REDCap: Research Electronic Data Capture.

#### Escalation Pathways for Child or Family Concerns

To ensure appropriate clinical governance, escalation pathways were developed with each study site with support from the steering committee (1) to support caregivers if they are distressed or unsafe when calling the personal navigator related to tier 4 of the eHub and (2) to support eHub personal navigation phoneline staff.

#### Cross-Sectoral Service Providers

We will purposively recruit service provider participants who meet the inclusion criteria (listed below) within each study site to participate in semistructured interviews at 6 months from the eHub first going live. Site leads at the 3 trial sites will provide access to individual service provider contact details who may wish to take part. We will then directly approach these primary care, mental health, health, welfare, and community providers to take part, ensuring that they meet the inclusion criteria and consent to be involved in the evaluation. Many of these service providers are represented through networks that we have existing relationships within Wyndham Vale, Fairfield, and Marrickville, such as Wyndham Child and Family Alliance (Victoria) and the Local Council Vulnerable Children’s Group (New South Wales). Potential participants will be sent a personalized email of invitation to participate in qualitative interviews at the 6-month time point with information about the details of the study objectives and providing the service provider participant information sheet.

The cross-sectoral service provider inclusion criteria are as follows: adults aged 18 years or older; work within the study intervention areas—Marrickville, Fairfield, or Wyndham Vale in health, or social service located at the Marrickville Community Health Service, Karitane in Fairfield or IPC Community Health Service in Victoria; and provide verbal informed consent.

### Baseline Data Collection: Prospective Cohort Caregiver Baseline Survey

For those who consent to be involved in the eHub evaluation, when accessing the eHub for the first time, caregivers’ baseline data will be collected via an online survey, which includes the research measures outlined in Table 2. This online survey will be built into a secure online portal (REDCap) [25,26] through the eHub as outlined in Figure 3. If consented families do not complete the baseline questionnaire, they will be contacted by a research assistant by phone, email, or text to complete.

**Table 2 table2:** Study activities and timeline.

Activity	Timeline
Funding and concept development	December 2021
User-centered design and minimum viable product development	June 2022 to December 2023
Ethics approval	June 2023
Participant recruitment commenced	February 2024
6-Month evaluation period per participant	February 2024 to November 2024
Quantitative and qualitative data collection	February 2024 to February 2025
Data analysis	February 2025 to May 2025
Dissemination of findings	2026

**Figure 3 figure3:**
[figure not shown]
Evaluation overview. PDSA: Plan-Do-Study-Act.

### Data Collection Throughout the eHub Study

#### Data Analytics on eHub Users

eHub metadata and digital analytical data on participants’ average session length and frequency, page use, and tiers of service use when using the eHub, as well as satisfaction scores and responses to short online surveys and questionnaires, will be collected for any users of the eHub using Google Analytics and Hotjar (Contentsquare; a web-based feedback poll that pops up on the eHub screen during an episode of use). Additionally, brief demographic data, including postcode and country of birth of user, will be collected. Tables 3 and 4 show the primary and secondary evaluation objectives and quantitative and qualitative data collected in parallel and integrated during data analysis and interpretation.

**Table 3 table3:** Primary evaluation outcomes and associated measures.

Primary outcomes: eHub^a^ implementation outcomes			Measure
**eHub access**			
	Reach: What is the proportion of caregivers within each site who access the eHub?	Data analytics on eHub users: Proportion of people who have accessed the eHub (numerator) among families that have children younger than 15 years of age based on Australian Bureau of Statistics reports for each site (denominator).	
	Coverage: Is the eHub reaching the intended audience of priority families (defined by residential socioeconomic disadvantage [SEIFA^b^ IRSD^c^ score in the lowest quintile or quartile?] and parental country of birth [parents born overseas?])	Data analytics on eHub users: User visits to each tier mapped against their demographic data including suburb to determine socioeconomic disadvantage, based on SEIFA scores and nomination of whether user was born overseas. This indicator measures the proportion of vulnerable families with children younger than 15 years who have accessed the eHub. Vulnerability is based on caregiver demographics—such as postcode (linked to SEIFA) and country of birth—compared to ABS caregiver data. The numerator is the number of vulnerable families who accessed the eHub, and the denominator is the total number of vulnerable 1- and 2-parent families with children younger than 15 years.	
**eHub use**			
	Engagement: Are families engaging with the eHub?	Data analytics on eHub users: Do caregivers passively use the eHub? Page hits, links opened to information, services within each tier of the eHub, and actively use the eHub, that is, searches undertaken through tiers 2 and 3 and clicking through to tier 4 support. eHub user data will include: Length of time on site or session length Visits or time per critical feature Interactions with filters Number of engaged sessions and engagement rate Engaged sessions per user or IP address Average engagement time Views per session or user	
	Acceptability: Do caregivers view the eHub as satisfactory?	Data analytics on eHub users: Pop-up surveys on satisfaction, Did you find what you were looking for? Or Was this useful? (Thumbs up or down or smiley or sad face) Survey (6 months): Satisfaction with content, delivery, level of support provided, credibility.	
	Adoption: To what extent can caregivers find and use information, services, and supports on the eHub?	Prospective cohort survey and interview (6 months): Did caregivers find the information provided useful for their needs? Were caregivers able to find an appropriate service or information to support their or their child’s needs? Did caregivers use or intend to use the strategies provided in the information? Changes to caregivers’ behavior (eg, help-seeking and implementing new strategies)	
	Appropriateness: Do caregivers perceive the eHub as useful and relevant? Did the caregiver feel reassured or supported by the information or services provided?	Prospective cohort survey (6 months): Perceived fit, relevance, compatibility, suitability, usefulness, practicability.	
	Barriers and enablers: Accessing and using information, services, and supports on eHub?	Prospective cohort caregiver and service provider qualitative interviews (6 months).	

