#### Continuous Learning and Improvement of the eHub Throughout Evaluation

Members from each evaluation site will form a project team alongside researchers to identify and respond to barriers for caregivers in accessing and engaging with the eHub. Using implementation science activities, the team will conduct 2-3 short Plan-Do-Study-Act quality improvement cycles [33] over the 6 months of implementation, including review of caregiver satisfaction with the navigation processes and content and whether caregivers are progressing to higher tiers of support. These short learning cycles will allow agile minor improvements of the eHub.

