#### Prospective Cohort Caregiver and Cross-Sectoral Service Provider Semistructured Interviews

Caregivers (n=15-20 in total) and intersectoral service providers (n=15-20 in total) from the evaluation sites will be invited to participate in individual semistructured interviews at 6 months after eHub implementation. Interviews will be conducted by web-conferencing platform (Zoom; Zoom Video Communications). Participants will be invited to provide their perspectives on barriers and enablers of using the eHub, such as were caregivers’ needs satisfied by using the eHub? Was the eHub able to support their unmet social needs? Did caregivers use or intend to use strategies provided in information sourced on the eHub? And were there changes to caregivers’ behavior (eg, help-seeking and implementing new strategies)? (see Multimedia Appendix 1 for interview guide). Participants will be invited to expand on any points they feel are important, and the interviewer may ask follow-up questions to elicit further details. The research assistant will be trained and experienced in qualitative methods; the interviews are expected to last between 20 and 30 minutes.

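### Engagement and pop-up Acceptability are asked about families and caregivers but measured on any eHub user, with no named item that identifies caregivers

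*Protocol article*

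**What the plan says.** The eHub use block of Table 3 (primary outcomes) asks "Engagement: Are families engaging with the eHub" and "Acceptability: Do caregivers view the eHub as satisfactory". The measure for the first is headed "Data analytics on eHub users: Do caregivers passively use the eHub". It lists page hits, links opened, session length, filter interactions, engaged sessions and engagement rate, with engaged sessions counted per user or per IP address.

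Acceptability has two sources. One is "Data analytics on eHub users: Pop-up surveys on satisfaction, Did you find what you were looking for", answered on screen. The other is "Survey (6 months): Satisfaction with content, delivery, level of support provided, credibility".

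On who supplies the analytics, the section Data Analytics on eHub Users says that they "will be collected for any users of the eHub using Google Analytics and Hotjar". The Recruitment section agrees: analytics cover everyone on the site, whether or not they take part in the evaluation, and those outside it need no consent because the data are unidentifiable. The user items named are postcode and country of birth, in a list that is left open. Recruitment also mentions demographic pop-up surveys without listing their items.

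The section Statistical Methods for All Quantitative Outcomes plans to describe proportions from eHub users and adds no restriction to caregivers. The Demographics row of Table 3 nevertheless treats the same metadata as describing the caregivers who access the eHub.

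**The concern.** The target population is families and caregivers; the measured population is every visitor. The article moves from one to the other without a step that makes them the same. Caregiver status is established in the REDCap baseline survey, so it is known for the cohort but not for site traffic in general.

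The site is open and widely advertised, including at primary care, community health and nongovernment hub sites and in schools, where professionals also see the posters and QR codes. Visits by people who are not caregivers are therefore plausible.

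Two conclusions are at stake. The first is the primary implementation result on engagement and satisfaction. The second is the economic result: the Health Economic Analysis section uses a cost per additional child or caregiver engaged, and the Cost row of Table 3 refers to the number of families engaged. If that number comes from the analytics, non-caregiver use enlarges the denominator and makes the eHub look cheaper per family.

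Role also differs from most analysis details in one respect. If it is not recorded when the session takes place, an analysis plan written later cannot restore it.

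**Working it through.** **Step 1: compare target and measure.**

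| Outcome | Asked about | Measured on | Named item showing caregiver status |
|---|---|---|---|
| Engagement | families, caregivers | any eHub user | none |
| Acceptability, pop-up | caregivers | any eHub user | none |
| Acceptability, 6-month survey | caregivers | evaluation cohort | yes, by enrolment |

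The mismatch affects the first two rows only.

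**Step 2: is there a figure to reproduce?** No. The article gives no target, test or expected value for Engagement or pop-up Acceptability. The sample size of 270 concerns service access in the cohort and does not bear on this point.

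**Step 3: what non-caregiver use would do.** Let s be the non-caregiver share of sessions, p_c the caregiver rate and p_o the rate in other users. The documents give none of these, so all values below are assumptions.

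- Reported rate = (1 - s) × p_c + s × p_o
- Bias in the rate = s × (p_o - p_c)
- Inflation of a session count = s / (1 - s)

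| s | p_c 40%, p_o 80% | p_c 60%, p_o 90% | p_c 60%, p_o 30% | Session count inflated by |
|---|---|---|---|---|
| 0% | 40% | 60% | 60% | 0% |
| 5% | 42% | 61.5% | 58.5% | 5.3% |
| 10% | 44% | 63% | 57% | 11.1% |
| 20% | 48% | 66% | 54% | 25% |
| 30% | 52% | 69% | 51% | 42.9% |

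For example, at s = 10% with 40% and 80%: 0.90 × 40% + 0.10 × 80% = 36% + 8% = 44%.

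The bias in the rate runs from +2 to +12 points in the first scenario, +1.5 to +9 in the second and -1.5 to -9 in the third. It is zero if nobody but caregivers visits. The sign depends wholly on whether other users engage more or less than caregivers. Counts can only rise. The same mixing formula applies to the share of favourable pop-up answers, again with unknown sign.

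**Step 4: rare features are the most sensitive.** The section on the eHub MVP expects 5% to 10% of users to need the personal navigator (tier 4). Assume that 5% of caregiver sessions click through to tier 4, that 5% of all sessions are by non-caregivers, and that half of those click through. The reported figure is 0.95 × 5% + 0.05 × 50% = 4.75% + 2.5% = 7.25%.

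**Step 5: the cost ratio.** If a share q of those counted as engaged are not caregivers, the reported cost per engaged unit is (1 - q) times the cost per engaged caregiver. At q = 10% it is 10% too low. This applies only if the engaged number is taken from the analytics. The Cost row names the cohort survey as its source, and the article does not say plainly which count is used.

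**The case against.** The strongest reply is that nothing in the article shows non-caregivers using the live site, and that internal-traffic filters and full pop-up item lists are set-up details which an article normally leaves to the full protocol or analysis plan. Much of this stands. The demographic list is open, so a role item may exist unreported, and the lack of a staff-traffic filter in the article is not a fault in itself. What remains is that the article itself fixes the question, the source and the population covered, and these disagree.

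Four stronger readings are tempting and are not supported:

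- **Staff sessions during the improvement cycles.** The article says "Members from each evaluation site will form a project team alongside researchers to identify and respond to barriers for caregivers", and a reader might infer repeated staff browsing that clusters around the Plan-Do-Study-Act cycles and imitates a gain. The section describes reviewing caregiver satisfaction and caregivers' progress through the tiers, not staff use of the site.
- **Service providers as users.** Of the interviews, it says "Participants will be invited to provide their perspectives on barriers and enablers of using the eHub". The example questions concern caregivers' needs and behaviour. Providers' own use is neither stated nor excluded.
- **Irreversibility.** A reader might take unidentifiable data to mean that staff sessions could never be removed. That phrase explains why consent is not needed. Table 3 lists a metric per user or IP address, so known team traffic could be filtered. Caregiver status of unknown visitors could not be recovered that way.
- **A definite upward bias.** This holds for counts but not for rates, as step 3 shows.

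It is also fair to say that these measures are descriptive, with no test attached, and that Acceptability has a second source, sent only to caregivers in the evaluation, which is untouched.

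**Conclusion.** The point holds as a mismatch between question and measure. Engagement and the pop-up part of Acceptability are primary outcomes about families and caregivers, answered with data on any user, and no named item tells the two apart. Any non-caregiver use would count as family engagement.

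How much such use there is cannot be learned from the documents. The shifts of -9 to +12 points in a rate, and 5.3% to 42.9% in a session count, rest entirely on assumed shares of 5% to 30% and assumed rates. They show sensitivity and are not estimates. It would go too far to say that professional use is being counted as family engagement; the supported statement is that it would be, if it occurs. The 6-month survey part of Acceptability is unaffected. This is a cheap improvement to measurement and labelling.

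**What to change.** 1. Add one tap to the existing demographic pop-up: parent or caregiver of a child aged 0-12, professional, or other.
2. Exclude known study-team and site-team traffic, and say so.
3. Report Engagement and pop-up Acceptability for all users, labelled as such, alongside self-identified caregivers with a site postcode. Give the share of unknown role with both.
4. Where role was not captured, call the measures all-user engagement and all-user satisfaction and draw no conclusion about families from them. Enrolment began in February 2024 and the article reports analysis from February to May 2025, so this step may be the only one open for the present data; the others then apply to any further rollout.
5. State which count of engaged families or caregivers enters the cost-effectiveness ratio. If it comes from the analytics, carry the all-user label into that result.

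The cost is one pop-up item, an analytics setting and some wording. The downside is that role will be missing for those who skip the pop-up, and those who answer are likely to be more engaged than those who do not. The caregiver-only figure is therefore itself selected and should stand beside the all-user figure, not replace it.
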